## 14.2 Secondary efficacy endpoint

The secondary endpoint is adhesion scores.

Evaluate adhesion scores through the following surveys at screening, 1 week and 6 weeks after thyroidectomy and application of the investigational product.

The secondary endpoint is evaluated by providing descriptive statistics (mean, standard deviation, median, minimum and maximum) by time point and group, and by providing descriptive statistics of the mean changes, compared to those at the screening, for each time point and each group after surgery. For the mean and mean variance of the intergroup at each time point, the unpaired t-test or Wilcoxon ranksum test is applied depending on whether the normality assumption is satisfied (Shapiro-Wilk test), and for the mean variance of the intragroup, the paired t-test or Wilcoxon signed rank test is applied. The significance level for each statistical analysis is  $p < 0.05$ .

Evaluate adhesion scores through surveys at screening, 1 week and 6 weeks after thyroidectomy and application of the investigational product. Score each clinical symptom for all questionnaires on a scale of 0 to 10. The higher the score, the more severe the adhesion [24,27].

|                                      |                                                                                                                                                                                                                                                                                            |
|--------------------------------------|--------------------------------------------------------------------------------------------------------------------------------------------------------------------------------------------------------------------------------------------------------------------------------------------|
| Subjective discomfort of patient     | 1. Do you have trouble swallowing your saliva?
2. Do you have difficulty swallowing water?
3. Do you have any difficulty in swallowing hard foods?
4. Are your neck wrinkles abnormal in your own opinion?                                                                        |
| Objective evaluation of investigator | 5. Are the wrinkles on the neck symmetrical and natural when the patient is at rest?
6. Are the wrinkles on the neck symmetrical and natural when the patient is at neck extension?
7. What is the degree of inflammatory response or scar formation based on the surgical findings? |

What is the neck extension? : A condition in which the subject's jaw is usually directed upward at 30 to 45 degrees from the horizontal so as not to be uncomfortable when the subject extends his/her neck

### 14.3 Analysis set

In the efficacy analysis of this clinical trial, the main analysis is the mITT set, and the PP set is additionally analyzed. The analysis for the safety is ITT set.

- ITT Set: An analysis set targeting for subjects who have received treatment at least once with an investigational product, among all subjects enrolled in this clinical trial
- Modified ITT Set: An analysis targeting for subjects who have received treatment at least once with an investigational product and participated in the primary efficacy endpoint evaluation, among all subjects enrolled in this clinical trial
- PP set: An analysis targeting for subjects who completed the study in accordance with this protocol without any significant violation of the protocol among ITT set

The exclusion criteria from the PP set because it is considered a serious violation of the protocol is as follows.

- 1) Violation of inclusion/exclusion criteria
- 2) Administration of drugs prohibited from concurrent use during the clinical trial
- 3) Other cases where it can be considered a serious violation of the protocol

### 14.4 Treatment of missing data

If there is a missing data in the analysis of the Modified ITT set for efficacy evaluation, the primary endpoint does not require a separate calibration according to the definition of the main analysis set, and the secondary endpoint is analyzed within the data observed at each time point and alternative processing for missing value is not planned. However, if the missing data is more than

10% of the analysis data during the secondary efficacy evaluation, apply the Repeated Mixed Model considering the missing data and present the results of additional analysis.

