### 13.2 Management of discontinuation

- 1) If the clinical trial is discontinued, the principal investigator shall collect and deliver the Case Report Form, the clinical trial progress status and results of the subject of which have progressed to the point where the study was discontinued to Sponsor. All study-related data (Case Report Form and the investigational product) shall be returned to the sponsor. Subjects whose the clinical trial has been discontinued shall be included in statistical processing for safety and efficacy evaluation.
- 2) If the clinical trial is terminated early or temporarily discontinued, the principal investigator shall immediately inform the subjects and ensure that appropriate measures and follow-up are carried out. And the principal investigator shall notify the Institutional Review Board of that in writing.

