### **13.3 Criteria for drop out**

- 1) Where a subject or his/her legal representative requests to stop participating in the clinical trial
- 2) Where surgery, drugs, or other medical devices that may affect the safety or efficacy have been used in combination
- 3) Where serious side effects occur
- 4) Where the treatment method has not been performed properly
- 5) Where a subject fails to comply with the requirements presented in the consent form, thus affecting the evaluation
- 6) Where continuous observation is not possible due to the absence of a subject
- 7) Other cases where the investigator determines that there is a problem in conducting the clinical trial

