### **13.4 Management of drop out**

- 1) If a subject is dropped out, record and keep the reason for the drop out and the related data to the clinical trial progressed before the drop out.
- 2) If a subject failed to visit during the study, check the subject's health condition and clarify the reason.
- 3) The subject dropped out shall be included in statistical processing when evaluating the safety and efficacy.

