### **14.1 Primary efficacy endpoint**

For the primary endpoint of this clinical trial, score the esophageal movement scores evaluated by marshmallow esophagography at 6 weeks after surgery into four grades (0, 1, 2, and 3). The primary endpoint is evaluated by providing the frequency, proportion, mean, standard deviation, median, minimum and maximum of the esophageal movement scores and by using the one-sided 97.5% confidence interval for the difference in the mean score of the 'esophageal movement' between the two groups (test group - control group) to determine whether the effect of the new treatment is non-inferior to the existing treatment. That is, if the lower limit of the one-sided 97.5% confidence

interval is greater than  $-0.1$ , which is the limits of non-inferiority ( $-\delta$ ), it is judged that 'the test group is non-inferior to the control group.'

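### The main efficacy analysis drops treated subjects without the 6-week esophagography and declares missing outcomes to need no handling, against sections 13.2 and 13.4; outcome-related loss that differs between arms would bias the result unseen

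*Protocol*

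**What the plan says.** - **Endpoint and rule (Protocol 14.1).** The primary endpoint is a 0 to 3 score, higher being better, measured once, at 6 weeks. Non-inferiority is judged "using the one-sided 97.5% confidence interval for the difference in the mean score of the 'esophageal movement' between the two groups", with the lower limit to lie above -0.1.
- **Main set (14.3).** The main efficacy set is the modified ITT set: treated subjects who also "participated in the primary efficacy endpoint evaluation, among all subjects enrolled in this clinical trial". The per-protocol set is additional and requires study completion. The ITT set, which here means all treated subjects, is assigned to safety only.
- **Missing data (14.4).** For the modified ITT analysis, "the primary endpoint does not require a separate calibration according to the definition of the main analysis set". The one model offered for missing data, a repeated mixed model when more than 10% is missing, is for the secondary endpoint.
- **Discontinuation (13.2).** Discontinued subjects "shall be included in statistical processing for safety and efficacy evaluation".
- **Drop-out (13.4).** "The subject dropped out shall be included in statistical processing when evaluating the safety and efficacy".
- **Reasons for drop-out (13.3).** These include "Where serious side effects occur", use of other surgery, drugs or devices that may affect efficacy, and treatment not properly performed.

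**The concern.** The reasoning in 14.4 is circular. The set is defined by having the outcome, so missing outcomes vanish by definition, and their absence is then given as the reason why nothing need be done. Conditioning on the outcome being present does not deal with missing data; it takes them out of sight.

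The listed drop-out reasons could bear on swallowing at 6 weeks and could occur at different rates with two different products. The device is applied once, at surgery. A later drop-out therefore stops no exposure; what it puts at risk is the week-6 measurement.

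At stake is the non-inferiority claim. If poor results are lost more often, or are worse, in the test arm, the completers look more alike than the treated arms are. The per-protocol analysis shares the defect, so agreement between the two analyses would be no reassurance.

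**Working it through.** **1. The plan's own figure.** From Protocol 8.4: margin 0.1, SD 0.2, true difference 0, z-values 1.96 and 0.84.

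n = 2 × (1.96 + 0.84)² × 0.2² / 0.1² = 62.72 (printed as 62.8), so 63 per arm. Allowing for 10% drop-out, 63 / 0.9 = 70. The figures reproduce. The planning loss is 7 of 70 per arm.

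**2. Size of the bias.** Let d be the share missing in each arm, and g the number of grades by which the test arm falls further behind control among the missing than among completers. Then

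all-treated difference = completer difference - d × g.

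The protocol gives no outcomes for drop-outs, so g is an assumption.

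| Assumed g (grades) | Shift at d = 0.10 | Share of the 0.1 margin |
|---|---|---|
| 0 | 0 | none |
| 0.2 | 0.02 | one fifth |
| 0.5 | 0.05 | half |
| 1 | 0.10 | all |

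The gap needed for a full-margin shift is 0.1 / d: 2 grades at 5% loss, 1 grade at 10%, 0.67 grade at 15%. The only reference effect in the protocol is comparator against placebo, 2.93 - 2.73 = 0.2 grade.

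**3. Chance of a false claim.** Set the true all-treated difference to exactly -0.1, with 63 completers per arm. Assume that 7% of observed controls score 2 and the rest 3 (mean 2.93, the comparator mean in 8.4). The observed test arm then has 0.07 + 0.1 - 0.1g at grade 2. Summing over all pairs of binomial counts and applying a t-based one-sided 97.5% lower limit:

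| g | Test completers at grade 2 | P(claim non-inferiority) |
|---|---|---|
| 0 | 17% | 3.2% |
| 0.2 | 15% | 6.8% |
| 0.3 | 14% | 9.6% |
| 0.5 | 12% | 18% |
| 1 | 7% | 62% |

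With the planning SD of 0.2 and a normal approximation instead (standard error 0.2 × √(2/63) = 0.0356), gaps of 0, 0.3, 0.5 and 1 give 2.5%, 13%, 29% and 80%. The level depends on the assumed spread; the pattern does not.

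**4. How few unseen subjects matter.** Take 4 of 63 at grade 2 in each arm (mean about 2.94) and the rest at grade 3. The completer difference is 0 and the lower limit is -0.087, so non-inferiority is claimed. Now add 7 missing subjects per arm, with the missing controls all at grade 3:

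| Missing test subjects at grade 2 | Grade 2, test vs control | Difference | Lower limit |
|---|---|---|---|
| 0 of 7 | 4/70 vs 4/70 | 0 | -0.078 |
| 1 of 7 | 5/70 vs 4/70 | -0.014 | -0.097 |
| 2 of 7 | 6/70 vs 4/70 | -0.029 | -0.115 |

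Two subjects, one grade down each, reverse the conclusion. Their arm's missing mean would be 19/7 = 2.71, close to the 2.73 that the protocol quotes for placebo.

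**The case against.** **Loss alone moves nothing.** A reader might infer that 10% attrition by itself can shift the result by the whole margin. It cannot: the loss must be related to outcome and must differ between arms. The 10% is also a planning allowance used to go from 63 to 70, not a tolerated loss. This stands.

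**The full-margin case is extreme.** With observed means near 2.93, a one-grade gap puts essentially all missing test subjects in an abnormal grade while missing controls look like observed controls. Nothing in the protocol suggests that pattern. If missing test subjects merely did as placebo did, the shift would be 0.02. This stands too, so the 62% should be read only as the end of a range. It does not remove the point, because the two-subject example in step 4 needs a gap of only 2/7, about 0.29 grade.

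**Sensitivity analyses often sit in the SAP, which is not shown.** So the protocol does not support saying that no sensitivity analysis exists for this trial. The point is narrower: the protocol itself rules that no handling is needed and contradicts itself elsewhere.

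**The contradiction is partial.** It would be wrong to read 14.3 as excluding every drop-out. A dropped-out subject who has the 6-week test belongs to the modified ITT set. The conflict concerns those without it.

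**Conclusion.** The point holds in limited form. Sections 14.3 and 14.4 cannot be reconciled with 13.2 and 13.4 for a treated subject without the 6-week test, and the stated reason for doing nothing is unsound. This follows from the text without any assumption.

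The size of the harm is conditional. At 10% loss per arm the bias is 0.1 × g, from nothing at g = 0 to the full margin at g = 1. The probability of a false claim runs from about 3% to 62% over that range, given 7% of controls at grade 2. Both g and the 7% are assumptions, and the documents do not show that differential, outcome-related loss is likely. What they do show is a margin narrow enough for two unseen subjects to decide the conclusion, and no analysis in the protocol that would reveal it.

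**What to change.** 1. Delete the sentence in 14.4 saying that the primary endpoint needs no separate handling.
2. Reconcile 13.2 and 13.4 with 14.3 and 14.4, stating how subjects without a 6-week score enter the efficacy evaluation. Say explicitly that any 6-week score obtained from a dropped-out subject is used. Whether Visit 4 testing is done once a drop-out criterion is met is for the sponsor to settle in that reconciliation.
3. Keep the observed-case modified ITT analysis. Add a pre-specified analysis of all treated subjects (the protocol's ITT set) with a tipping-point analysis: worsen the missing test-arm scores step by step until the lower limit reaches -0.1, and report that shift.
4. Do not use the reason for loss as an imputation predictor, since it is undefined in completers. Week-6 adhesion scores are collected at the same visit as the esophagography and will usually be missing with it. With about 4 abnormal scores per arm (0.07 × 63 = 4.4), a within-arm imputation model would be too unstable to serve as the primary analysis.

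The cost is amended wording, a little more analysis work, and the possibility of a less favourable supporting result.

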#### **14.5 Analysis of demographic and basic data**

Examine demographic information on the mITT set. In the demographic and basic data of the subjects, continuous data (age, weight, height, blood pressure and pulse rate) shall be presented as descriptive statistics (the number of subjects observed, mean, standard deviation, median, minimum and maximum), and categorical data (gender, major medical history, drug history, smoking and drinking) as frequency and percentage. When comparing the demographic and basic data between the two groups, continuous data (age, weight, height, pulse rate) shall be compared by unpaired t-test or Wilcoxon ranksum test depending on whether the normality assumption is satisfied (Shapiro-Wilk test), and categorical data (gender, major medical history, drug history, smoking, drinking) shall be compared by Chi-square test (Fisher's exact test if the cell of which the expected frequency is not more than 5 exceeds 20% of the total).

### **15 Evaluation Standard of Safety Including Side Effects, Its Evaluation Method and Report Method**

#### **15.1 Definition of adverse event**

"Adverse Event (AE)" means any unintended sign (including abnormalities from laboratory test results, etc.), symptom or disease that occurs to a subject during the clinical trial, and is not necessarily causally related to the investigational product.

"Adverse Device Effect (ADE)" refers to any harmful and unintended reaction caused by the investigational product, and means an adverse event that cannot be denied a causal relationship with the investigational product.

"Unexpected Adverse Device Effect" refers to a difference in the aspect or degree of harm from that of the Adverse Device Effect based on available medical device-related information such as Investigator's Brochure or the attached documents of the medical device.

The followings are excluded from adverse events.

- 1) Medical or surgical treatment (ex: surgery, endoscopy, tooth extraction, appendectomy) ; The condition that caused this treatment is an adverse event.
- 2) Where any existing disease that was already present or found at the start of the clinical trial did not worsen after the treatment of the investigational product

- 3) Hospitalization for surgery to treat an existing disease that has not worsened scheduled before participating in the clinical trial
- 4) Hospitalization for medical examination
- 5) Optional hospitalization for cosmetic surgery

## **15.2 Definition of serious adverse event/adverse device effect (Serious AE/ADE)**

Serious adverse event/adverse device effect means a case that falls under any of the followings among adverse events or adverse device effects that occurred during the clinical trial.

- 1) Where death or life-threatening danger occurs
- 2) Where it is required to be hospitalized or extend the period of hospitalization
- 3) Where permanent, serious disability or serious hypofunction was resulted in
- 4) Where malformation or abnormality occurred in the fetus

## **15.3 Evaluation of adverse event**

Adverse events shall be evaluated by the principal investigator or the sub-investigator.

### **15.3.1 Severity evaluation**

If an adverse event occurs, it should be reported according to the following criteria for severity.

- Mild : A degree to which a subject can easily endure, without interfered with his/her normal daily life (or function) and with causing minimal discomfort
- Moderate : A degree to which it causes inconvenience to the extent that it significantly hinders the normal daily life (or function) of a subject
- Severe : A degree to which the normal daily life (or function) of a subject is impossible; a degree to which a subject is unable to continuously participate in the study; or a degree to which a subject needs to be treated or hospitalized

### **15.3.2 Assessment of causal relationship with investigational product**

In the event of an adverse event, the investigator shall evaluate whether it has the relevance with the investigational product based on the following criteria. And, the investigator's opinion should be described.

#### · Definitely related

- The temporal sequence between the use of the investigational product and the onset of the adverse event is reasonable.
- It is most likely that the adverse event has occurred due to the use of the investigational product than any other reason.

- When stopping using the investigational product, the adverse event disappears.
- Reusing the investigational product (only if re-use is allowed), the results are positive.
- The adverse event is consistent with previously known information about the investigational product or medical devices of the same family.

· Probably related

- There is evidence of using the investigational product.
- The temporal sequence between the use of the investigational product and the onset of the adverse event is reasonable.
- It is more likely that the adverse event has occurred due to the use of the investigational product than any other reason.
- When stopping using the investigational product, the adverse event disappears.

· Possibly related

- There is evidence of using the investigational product.
- The temporal sequence between the use of the investigational product and the onset of the adverse event is reasonable.
- It is judged that the adverse event is due to the use of the investigational product at the same level as other possible causes.
- When stopping using the investigational product (if performed), the adverse event disappears.

· Probably not related

- There is evidence of using the investigational product.
- There is a more probable cause of the adverse event.
- When discontinuing the use of the investigational product, the results are negative or ambiguous (if performed).
- Reusing the investigational product (only if re-use is allowed), the results are negative or ambiguous.

· Not related

- The investigational product was not used.
- The temporal sequence between the use of the investigational product and the onset of the adverse event is not reasonable.
- There are other obvious causes of the adverse event.

· Unknown

- Information is insufficient or conflicting and cannot be judged. And the information cannot be supplemented or verified.

## **15.4 Evaluation standard of safety**

In this clinical trial, all undesirable medical findings that develop symptoms that were not observed

before the application of the investigational product are classified as adverse events. The predicted side effects are also classified as adverse events, and the severity of adverse event is classified as mild, moderate, and severe.

#### 15.4.1 Predicted side effect

- 1) Side effects associated with general surgery : Abscess, cellulitis, wound, dermal necrosis, swelling, hematoma, cardiovascular disease, hypertension, ischemia, thrombus, embolism, hemorrhage, complications related to anesthesia, pulmonary complications, nerve/muscle damages, etc.
- 2) Side effects associated with the use of anti-adhesion product : Infection, allergic reaction, pain, and inflammatory reaction
- 3) Side effects associated with total thyroidectomy : Hypoparathyroidism, recurrent laryngeal nerve injury, hemorrhage, infection, superior laryngeal nerve paralysis, dyspnea, etc.

### 15.5 Safety evaluation method (statistical analysis method)

The analysis for the safety is ITT set. For all side effects reported during the study, determine the number of patients with the side effects, the rate and the number of occurrence by group. Analyze the incidence of adverse events between the test and control groups using the chi-square test (or Fisher's exact test).

Present descriptive statistics for adverse events by observation point and group. Among the results of hematological test, serum biochemical test and urinalysis, continuous data shall be presented as descriptive statistics (the number of subjects observed, mean, standard deviation, median, minimum and maximum), and categorical data as frequency and percentage. Since the occurrence of somatic signs is categorical data, it shall be presented as frequency and percentage. If necessary, these data can be compared and evaluated by applying statistical analysis (chi-square test, Fisher's exact test, unpaired t-test, paired t-test, etc.). The significance level of each statistical analysis is  $p < 0.05$ .

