| Title                            | Double-blind, Multi-center randomized, prospective confirmatory clinical study to evaluate the efficacy and safety of MegaShield using for anti-adhesion after total thyroidectomy                                                                                                                                                                                                                                                                                                                                                                                                                                                                                                                                                                                                                                                                                                                 |
| Purpose                          | The purpose of this study is to evaluate the anti-adhesion effect of MegaShield after thyroidectomy by applying MegaShield or Guardix-SG to patients who have undergone total thyroidectomy to compare anti-adhesion effect and safety.                                                                                                                                                                                                                                                                                                                                                                                                                                                                                                                                                                                                                                                            |

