| Study Period                     | 32 months from the date of approval (April 2018 ~ December 2020)                                                                                                                                                                                                                                                                                                                                                                                                                                                                                                                                                                                                                                                                                                                                                                                                                                   |
| Number of Subjects               | 140 subjects (70 in each of the test group and the control group)                                                                                                                                                                                                                                                                                                                                                                                                                                                                                                                                                                                                                                                                                                                                                                                                                                  |

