|  | 
subjects enrolled in this clinical trial
 
 
· Modified ITT Set: An analysis targeting for subjects who have received treatment at least once with an investigational product and participated in the primary efficacy endpoint evaluation, among all subjects enrolled in this clinical trial
 
· PP set: An analysis targeting for subjects who completed the study in accordance with this protocol without any significant violation of the protocol among ITT set
 
 
The primary endpoint is evaluated by providing the frequency, proportion, mean, standard deviation, median, minimum and maximum of the esophageal movement scores and by using the one-sided 97.5% confidence interval for the difference in the mean score of the 'esophageal movement' between the two groups to determine whether the effect of the new treatment is non-inferior to the existing treatment.
 
The secondary endpoint is evaluated by providing descriptive statistics (mean, standard deviation, median, minimum and maximum) by time point and group, and by providing descriptive statistics of the mean changes, compared to those at the screening, for each time point and each group after surgery.
 
The safety is analyzed on the ITT set. For all adverse events reported in the study period, the number of subjects with adverse events, the proportion, and the number of cases shall be calculated by group. The incidence of adverse events in the test group and control group shall be analyzed by chi-square test (Fisher's exact test).
 |

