## 6. Purpose and background

### 6.1 Purpose of clinical trial

It is widely known that postoperative administration of anti-adhesion has an effect of preventing adhesion on surgical sites and surrounding tissues. In this clinical trial, the anti-adhesion effect and safety are compared and evaluated by applying either MegaShield or Guardix-SG after thyroidectomy to patients who have undergone total thyroidectomy in order to evaluate the postoperative anti-adhesion effect of MegaShield.

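### The comparative safety aim rests on a chi-square/Fisher test of no difference, with no effect estimate or interval; at 70 per arm a non-significant result says little about uncommon events

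*Protocol*

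**What the plan says.** The Purpose entry of the protocol summary says the two products are applied "to compare anti-adhesion effect and safety". Section 6.1 repeats the aim: "the anti-adhesion effect and safety are compared and evaluated by applying either MegaShield or Guardix-SG".

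Section 15.5 sets the method, on the ITT set (treated subjects). For side effects it asks the analyst to "determine the number of patients with the side effects, the rate and the number of occurrence by group", and then: "Analyze the incidence of adverse events between the test and control groups using the chi-square test (or Fisher's exact test". The summary says the same: "The incidence of adverse events in the test group and control group shall be analyzed by chi-square test (Fisher's exact test". Section 15.5 sets p < 0.05 for each analysis. It also allows optional further tests on the safety data at the same level.

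What counts as an adverse event is broad. Section 15.4 says: "The predicted side effects are also classified as adverse events". Section 15.4.1 lists those effects in three groups: general surgery, the anti-adhesion product class (item 2), and total thyroidectomy.

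For efficacy the protocol works differently: section 14.1 compares a confidence limit for the mean difference with -0.1. Section 8.4 derives the sample size from that comparison alone.

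**The concern.** A test of no difference can show that two products differ. It cannot show that they are similar, and it does not say how large a difference the data leave open. Here similarity is the favourable outcome for safety, and the planned inferential output for that outcome is a p-value above 0.05. Because the sample size ignores safety, such a p-value may reflect little more than 70 patients per arm.

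At stake is the safety half of the trial's conclusion. A report that follows section 15.5 to the letter gives counts, rates and a p-value. The planned comparison itself would not display how much excess harm remains compatible with the data.

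**Working it through.** **Inputs from the protocol.** Size: "140 subjects (70 in each of the test group and the control group". Safety set: treated subjects (section 14.3), so at most 70 per arm. Level 0.05 (section 15.5); sidedness is not stated and is taken as two-sided.

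**Inputs that are assumptions.** All event rates, because the protocol gives none; the background rate of surgical events; and independence of background and product events.

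**Step 1: the plan's own sample size.** n = 2(1.96 + 0.84)² × 0.2² / 0.1² = 2 × 7.84 × 0.04 / 0.01 = 62.7 (62.8 with unrounded z values, as printed), so 63; then 63 / 0.9 = 70 per arm. The figure reproduces, and no safety quantity enters it.

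**Step 2: chance of missing a real difference, one event type tested alone.** For true rates p₁ and p₂, the miss probability is the sum, over all tables (x₁, x₂) with p ≥ 0.05, of Bin(x₁; 70, p₁) × Bin(x₂; 70, p₂). The first figure uses the uncorrected chi-square test and the second uses Fisher's test.

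| Control vs test | Missed, chi-square | Missed, Fisher |
|---|---|---|
| 5% vs 10% | 80% | 89% |
| 10% vs 20% | 62% | 70% |
| 15% vs 30% | 42% | 51% |
| 20% vs 40% | 25% | 32% |
| 2% vs 6% | 79% | 92% |
| 5% vs 15% | 48% | 59% |
| 10% vs 30% | 14% | 19% |

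The miss rate falls to 50% at these control rates:

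- doubling: about 13% (chi-square) or 15.5% (Fisher);
- tripling: about 5% (chi-square) or 6% (Fisher).

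**Step 3: if the test is applied to subjects with any adverse event.** With background rate b and an independent product event rate p, the any-event rate is 1 - (1 - b)(1 - p). For b = 40%:

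- 10% becomes 1 - 0.6 × 0.9 = 46%, and 30% becomes 1 - 0.6 × 0.7 = 58%. Missed 70% (chi-square) to 76% (Fisher), against 14% to 19% when tested alone.
- 10% vs 20% becomes 46% vs 52%. Missed 89% to 92%.

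Very large effects still show. With b = 20%, 15% vs 45% becomes 32% vs 56% and is missed in only 18% to 22% of trials.

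**Step 4: what an interval would add.** Take 11/70 vs 4/70, a difference of 10.0 points.

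- Pooled rate 15/140 = 0.107; chi-square = 0.1² / (2 × 0.107 × 0.893 / 70) = 3.66, p = 0.056; Fisher p = 0.099.
- Wilson limits are 0.090 to 0.260 for 11/70 = 0.157, and 0.022 to 0.138 for 4/70 = 0.057.
- Newcombe lower limit: 0.100 - √[(0.157 - 0.090)² + (0.138 - 0.057)²] = -0.005.
- Newcombe upper limit: 0.100 + √[(0.260 - 0.157)² + (0.057 - 0.022)²] = 0.208.

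So a result labelled not significant leaves an excess of up to 20.8 points open. With equal counts, 4/70 vs 4/70, the interval is -8.8 to +8.8 points.

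**The case against.** The strongest reply has four parts.

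- **Convention and the SAP.** Descriptive safety tables with a chi-square or Fisher test are common in trials sized for efficacy, and interval columns are often left to the SAP, which is not shown. This stands in part: an absent interval alone would not be a finding. But the protocol itself selects and fixes the inferential method, in two places, for an aim that it calls comparative. The choice made is open to criticism.
- **No rule equates non-significance with safety.** This stands. A reader might infer that the plan declares the products equally safe when p > 0.05. The protocol says no such thing. The defect is an uninformative method, not a wrong decision rule.
- **The data are not hidden.** This also stands. Counts and rates by group are required, so a reader could compute an interval afterwards. That does not make it part of the planned comparison.
- **Weak power is not universal.** This stands too. It is tempting to say the test misses a doubling or tripling at least half the time. Without a stated event rate that cannot be claimed, and for 10% vs 30% or 20% vs 40% it is false.

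It is equally tempting to say the test is certainly on overall incidence and that surgical events swamp the signal. Section 15.5 can be read either per event or overall, and the dilution depends on an assumed background rate and independence.

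**Conclusion.** The point holds in limited form. The protocol sets a comparative safety aim and answers it with a test of no difference, without an effect estimate or interval, in a trial whose size was chosen for another endpoint. For uncommon events, a non-significant result is weak support for comparable safety: at 70 per arm the chi-square test misses half or more of doublings from control rates up to about 13% and of triplings up to about 5%, with slightly higher limits under Fisher. Commoner, larger effects would usually be found if tested alone. If the test is on any adverse event, the weak range is wider. All of these figures rest on assumed event rates, on two-sided testing and on a full 70 treated per arm. The change is worth making, because it is cheap and improves what can be concluded, but nothing here invalidates the design.

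**What to change.** In section 15.5 and the Statistics entry of the summary, make the risk difference (test minus control) with a two-sided 95% confidence interval (Newcombe or Miettinen-Nurminen) the basis of the safety comparison. Report it for subjects with:

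- any adverse event;
- any serious adverse event;
- any product-class effect in section 15.4.1 item 2;
- any adverse device effect as defined in section 15.1. Note that causality is judged by investigators, whereas section 10.1 describes only subjects and the independent evaluator as blinded.

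Keep the chi-square/Fisher p-value as descriptive, and state that p > 0.05 alone will not be reported as evidence of comparable safety. No numerical safety threshold is needed, because the interval shows what the data exclude.

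The cost is a few sentences and some extra table columns, with no new data or patients. The downside is less favourable wording, since even equal counts of 4/70 leave an excess of about 8.8 points open.
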